**7.2. Discussion of Design and Control**

Study Period I is designed to determine if subjects meet all of the inclusion criteria and none of the exclusion criteria. The screening interval may last between 5 to 28 days in order to accommodate the long washout period of some excluded medications, such as fluoxetine. Where no washout is required, qualified patients may enroll 5 days after they have completed all screening and laboratory assessments.

Study Period II is designed to assess the safety and efficacy of atomoxetine compared to placebo on signs and symptoms of ADHD in young adults over 12 weeks of therapy.

This study design uses a blinded randomization placebo lead-in period which blinds the patients and investigational sites to the start of active therapy. The rationale for blinding the start of active therapy is based on the experience of researchers at Lilly Research Laboratories and on the published literature which underscores the difficulties of detecting a true drug effect in the face of the typically sizable placebo response.

Consequently, efforts to satisfactorily maintain the double-blind nature of the study are of the utmost importance. Evidence suggests that using a 1-week, single-blind, placebo

lead-in period, a standard approach for antidepressant clinical trials, is of limited value in eliminating subjects most susceptible to volatile symptom rating and high placebo response rates (Trivedi et al. 1994).

This study design method blinds investigators and patients to the time of initiation of the active therapy. Blinding the time of initiation of the active therapy will ensure a more accurate baseline assessment, and therefore, will obtain more accurate evaluation for the treatment effect. The blinding of start of active study drug, as well as assignment of patients to treatment groups, will be maintained by use of an interactive voice response system (IVRS).

This protocol contains a description of the study design in sufficient detail to inform the investigators and staff personnel of the study goals and to ensure patient safety. Under no circumstances will investigators or staff personnel know the complete details of the study design. A separate document (IRB Supplement 1) contains a complete account of the study design. IRB Supplement 1 will be provided along with this protocol to investigators’ ethical review boards and regulatory agencies for review.

The starting dose of atomoxetine 40 mg/day (dosed BID) for 7 days during Study Period II was selected in order to improve tolerability for some patients who experience expected pharmacologic effects such as gastrointestinal upset. Further, this dosing strategy is within label and most closely mirrors clinical practice.

Study Period III is a 12-week open-label extension period available for patients completing SPII.

**8. Study Population**

After the completion of screening during Visit 1 and Visit 2, patients who are not excluded and continue to meet all of the inclusion criteria will be eligible to begin the double-blinded treatment period at the end of Visit 2.

Study participants should be instructed not to donate blood or blood products during the study and for 1 week following the study.

**8.1. Inclusion Criteria**

Patients are eligible to be included in the study only if they meet **all** of the following criteria:

[1] Currently meets DSM-IV™-TR criteria for ADHD as assessed by the ACDS.

Concomitant Axis I diagnoses that are also allowed (current - if diagnosed greater than 6 months immediately prior to Visit 1 - or lifetime) are specific phobias, Generalized Anxiety Disorder (GAD), and Social Anxiety

Disorder. Current or lifetime dysthymia is allowed if diagnosed greater than

2 years immediately prior to Visit 1.

[2] Patient’s CAARS-Inv:SV total ADHD symptom score cannot decrease by more than 25% between Visit 1  **and** Visit 2.

[3] Patients must have a CGI- ADHD-S score of 4 (moderate symptoms) or greater at both Visit 1  **and** Visit 2.

[4] Male or female outpatients 18 to 30 years of age at Visit 1.

[5] (Note: This inclusion criterion applies only to females of childbearing potential—those women not surgically sterilized and between menarche and

1 year post-menopause). Women of childbearing potential must test negative for pregnancy at the time of enrollment based on a serum pregnancy test and agree to use a reliable method of birth control (for example, use of oral contraceptives or Norplant®; a reliable barrier method of birth control: diaphragms with contraceptive jelly, cervical caps with contraceptive jelly, condoms with contraceptive foam; intrauterine devices; partner with vasectomy; or abstinence) during the study.

[6] Must have an ECG performed at Visit 1. The results of the screening ECG must be read and the results must be available to the investigator or qualified designee at Visit 1. If an ECG shows an abnormality meeting the criteria in the protocol, the guidelines in the attachment for excluding, discontinuing

the patient and contacting the sponsor should be followed. Patients with other abnormalities may be included at the discretion of the investigator; however, the Lilly physician monitor or designee must be notified.

[7] Must be able to swallow capsules.

[8] No evidence of cognitive impairment that would preclude adequate participation in the trial or ability to sign the informed consent document.

[9] Have been judged by the investigator to be reliable to keep appointments for clinic visits and all tests, including venipuncture, and examinations required by the protocol.

[10] Must be able to communicate effectively with the investigator and study coordinator in English; specifically, patients must possess an educational level and degree of fluency of English that enables them to independently complete study tasks (for example, read and understand informed consent, complete self-rated study scales, etc.), and communicate suitably with the investigator and study coordinator as judged by the investigator. Further, patients must be willing to complete some questionnaires on a computer via the study website.

***8.1.1. Disease Diagnostic Criteria***

Pre-screening assessment conducted prior to a patient presenting at a clinical research site will include the ASRS v1.1. Clinical assessments conducted during the screening period will include clinical history, SCID-RV (First et al. 2000), and the ACDS v1.2.

**8.2. Exclusion Criteria**

Patients will be excluded from the study if they meet **any** of the following criteria:

[11] Are investigator site personnel directly affiliated with this study and/or their immediate families. Immediate family is defined as a spouse, parent, child, or sibling, whether biological or legally adopted.

[12] Are Lilly employees.

[13] Are currently enrolled in, or discontinued within the 30 days prior to Visit 1 from, a clinical trial involving an off-label use of an investigational drug or device (other than the study drug used in this study), or concurrently

enrolled in any other type of medical research judged not to be scientifically

or medically compatible with this study.

[14] Patients who have not responded to an adequate trial of atomoxetine, or have previously been adequately treated with atomoxetine, who have experienced intolerable side effects while receiving atomoxetine, OR have previously completed or withdrawn from this study or any other study investigating atomoxetine.

[15] Initiation of psychotherapy, change in intensity of psychotherapy, cognitive behavioral therapy, supportive therapy, or other non-drug therapies (such as acupuncture or hypnosis) within 30 days immediately prior to Visit 1, or at any time during the study.

[16] Any of the following current DSM-IV-TR™ Axis I diagnoses including: patients diagnosed with major depressive disorder (MDD), panic disorder, post-traumatic stress disorder, or an eating disorder within the past year immediately prior to Visit 1.

Any of the following current or lifetime DSM-IV-TR™ Axis I diagnoses including: patients diagnosed with obsessive-compulsive disorder, bipolar affective disorder, or psychosis.

[17] Are pregnant or are breastfeeding.

[18] Have organic brain disease, for example, dementia, or traumatic brain injury residua. Have a history of any seizure disorder (other than febrile seizures) or patients who have taken (or are currently taking) anticonvulsants for seizure control.

[19] Have a history of severe allergies to more than 1 class of medications or multiple adverse drug reactions.

[20] Patients judged clinically to be at serious suicidal risk, or patients, in the opinion of the investigator, are poor medical or psychiatric risks for study completion.

Specifically, a **baseline score of 3 or greater** on Item 10 (Suicidal Thought)

of the MADRS scale **is an automatic exclusion** from the trial.

A **post-baseline** spontaneous report of suicidal thoughts or behavior at any visit OR a score of **2 or greater** on Item 10 (Suicidal Thought) of the MADRS scale at Visit 4, 6, and 9 will require the administration of the Columbia Suicide-Severity Rating Scale.

If in the PI’s clinical judgment, the PI determines the patient to *not* be at serious suicide risk (using Columbia scale as a tool), the patient may continue in the study.

If in the PI clinical judgment, the PI determines the patient to be at serious suicidal risk, the risk should be addressed immediately using the PI’s best clinical judgment. Further,

a. serious suicidal risk is exclusionary and the patient must be discontinued, and

b. the site must contact and inform the sponsor of the event within 24 hours by contacting the Clinical Research Associate (CRA) who will then contact the Lilly study physician.

[21] Are currently using alcohol, drugs of abuse, or any prescribed or over-the- counter medication in a manner which the investigator considers indicative of DSM-IV-TR™ criteria for substance abuse or dependence.

If the urine drug screen is positive for any substance, the investigator should discontinue the patient *only* if the substance is being used in a manner indicative of DSM-IV-TR™ criteria for substance abuse or dependence OR

if the substance is on the excluded medication list (Protocol Attachment

LYDZ(b).3) and the patient cannot or will not discontinue the medication.

[22] Are taking any psychotropic medication on a regular basis, including health- food supplements that the investigator feels have central nervous system activity (for example, St. John’s Wort, melatonin, etc.).

[23] Have a current diagnosis of uncontrolled hyper- or hypothyroidism. Patients with an initial abnormal TSH screen should be evaluated with additional

thyroid tests through a local lab to determine eligibility for the study or the need for treatment prior to re-screening and participation in the study. **Note:** Patients previously diagnosed with hyperthyroidism or hypothyroidism that have been treated on a stable dose of thyroid supplement for at least the past

3 months immediately prior to Visit 1, have medically appropriate TSH

concentrations, and are clinically euthyroid are allowed.

[24] Have any medical condition that would increase sympathetic nervous system activity markedly (for example, catecholamine-secreting neural tumor), or who are taking a medication on a daily basis (for example, albuterol, inhalation aerosols, pseudoephedrine), that has sympathomimetic activity. Such medications can be taken on an as-needed basis.

[25] Have used monoamine oxidase inhibitors (MAOIs) during the 2 weeks

(14 days) prior to Visit 2.

[26] Have a current diagnosis of uncontrolled hypertension. For the purposes of this protocol, hypertension will be defined as average systolic or diastolic blood pressure, measured on at least 2 separate occasions, greater than or equal to 140/90. Patients whose blood pressure is controlled with non- excluded medication are eligible for inclusion.

[27] Who have narrow-angle glaucoma.

[28] Have a history of difficulty starting a stream of urine or other symptoms suggestive of prostate enlargement, or other evidence of urinary hesitancy on clinical history.

[29] Who anticipate a move outside the geographic range of the investigative site after beginning active treatment, or who plan extended travel inconsistent with the recommended visit interval during Study Period II.

[30] Serious medical illness, including any cardiovascular, hepatic, renal, respiratory, hematologic, endocrinologic, or neurologic disease, or clinically significant laboratory abnormality that is not stabilized or is anticipated to require hospitalization within 6 months, in the opinion of the clinical investigator. Clinically significant laboratory abnormalities are those that, in the judgment of the investigator, indicate a serious medical problem.

[31] Have had transcranial magnetic stimulation (TMS) or history of psychosurgery, electroconvulsive therapy (ECT), or vagus nerve stimulation within 12 months immediately prior to Visit 1.

[32] Are unsuitable in any way to participate in this study, in the opinion of the investigator.

***8.2.1. Rationale for Exclusion of Certain Study Candidates*** Exclusion Criteria [11] and [12] reduce the potential bias that may be introduced at the study site. Exclusion Criterion [13] eliminates drugs that cannot be mapped to a standard drug dictionary, or for which little data are known to analyze the potential relationship of adverse events or drug interactions. Exclusion criteria [14-17], [21-23], and [29] eliminate conditions, situations, or medications that may interfere with protocol compliance or confound the study data. All other exclusion criteria [18-20], [24-28], and [30-32] are present to ensure the safety of study patients

No patients are excluded from participation based on race, ethnicity, or gender. Patients

at serious suicidal risk are excluded to ensure patient welfare. Exclusions of patients with specific medical conditions and/or patients taking specific medications are listed because of potential for interaction of those conditions or medication with known or potential effects of atomoxetine. Patients taking certain psychoactive medications or drugs of

abuse noted in the exclusion criteria are excluded because of the potential for these

medications to confound interpretation of the efficacy results.

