**8.3. Discontinuations**

***8.3.1. Discontinuation of Patients***

The criteria for enrollment must be followed explicitly. If a patient who does not meet enrollment criteria is inadvertently enrolled, that patient should be discontinued from the study, and Lilly or its designee must be contacted.

In addition, patients will be discontinued from the study drug and from the study in the following circumstances:

• Enrollment in any other clinical trial involving an off-label use of an investigational drug or device or enrollment in any other type of medical research judged not to be scientifically or medically compatible with this study.

• If Exclusion Criterion [11-32] is observed, or develops, after entry or enrollment. In this case, the patient will be discontinued from the study at the next visit or sooner in the event of a safety exclusion criterion.

• The investigator decides that the patient should be withdrawn. If this decision is made because of a serious adverse event or a clinically significant laboratory value, the study drug is to be discontinued and appropriate measures are to be taken. Lilly or its designee is to be alerted immediately. Refer to Section 10.3, Safety Evaluations.

• The patient or attending physician requests that the patient be withdrawn from the study.

• The patient, for any reason, requires treatment with another therapeutic agent that has been demonstrated to be effective for treatment of the study indication. In this case, discontinuation from the study occurs prior to

introduction of the new agent.

• The investigator or Lilly, for any reason, stops the study or stops the patient's participation in the study.

Patients who discontinue the study early will have end-of-study procedures performed as shown in the Study Schedule (Protocol Attachment LYDZ(b).1).

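### Pregnancy is sorted outside the safety exclusion criteria, so the discontinuation rule points to stopping at the next visit and nothing requires study drug to stop at once

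*Protocol*

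**What the plan says.** Criterion [17] in Section 8.2 excludes patients who are pregnant or breastfeeding. Section 8.2.1 gives the reason for each group of criteria. Criteria [11] and [12] guard against bias at the site, and [13] deals with drugs that cannot be mapped or are little known. Then: "Exclusion criteria [14-17], [21-23], and [29] eliminate conditions, situations, or medications that may interfere with protocol compliance or confound the study data". The rest are the safety group: "All other exclusion criteria [18-20], [24-28], and [30-32] are present to ensure the safety of study patients".

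Section 8.3.1 states that "patients will be discontinued from the study drug and from the study in the following circumstances", and one of those circumstances is that any of [11-32] is seen or develops after entry or enrolment. For that circumstance the timing is: "the patient will be discontinued from the study at the next visit or sooner in the event of a safety exclusion criterion". The section does not define a safety exclusion criterion and does not refer back to 8.2.1.

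Other places bear on pregnancy. Inclusion criterion [5] requires a negative serum test and reliable contraception. Section 10.3.1 asks for pregnancies to be reported and for fetal outcome data to be collected for drug safety evaluation. The Study Schedule (Attachment LYDZ(b).1, footnote h) requires a pregnancy test only at Visit 1; later tests are at the investigator's discretion.

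**The concern.** Whether a patient leaves at the next visit or sooner depends on whether the criterion she meets is a safety criterion. Section 8.2.1 is the only part of the protocol that says which criteria those are, and it places [17] elsewhere. A site that follows the written sorting could leave a patient on study drug until her next visit after her pregnancy is known.

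At stake is avoidable fetal exposure. Because testing is scheduled only at Visit 1, a pregnancy during the study may well come to light between visits. The longest gaps fall in Study Period III, when all patients receive open-label atomoxetine (Section 9.1.2). The placement also conflicts with the protocol's own handling of pregnancy as a safety matter in [5] and 10.3.1.

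**Working it through.** **Classification.** The groups in 8.2.1 are:

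| Group | Criteria |
| --- | --- |
| Bias | [11], [12] |
| Unmappable or little-known drugs | [13] |
| Compliance or confounding | [14-17], [21-23], [29] |
| Safety | [18-20], [24-28], [30-32] |

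Together they cover 11 to 32 with no gap and no overlap. The safety group is introduced as everything not already listed. So [17] is assigned to another group, not merely left off the safety list.

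**Is there an overriding instruction?**

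- Suicidal risk, [20], has its own urgency: if "the PI determines the patient to be at serious suicidal risk, the risk should be addressed immediately".
- If the investigator withdraws a patient for a serious adverse event or a clinically significant laboratory value, 8.3.1 adds that "the study drug is to be discontinued and appropriate measures are to be taken".
- For pregnancy, the text on the entry test, contraception, reporting and test schedule contains no instruction to stop drug at once.

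**Longest wait.** Visit windows come from the Study Schedule.

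| Interval | Window (days) | Target (days) |
| --- | --- | --- |
| Visits 2-3 | 10-18 | 14 |
| Visits 3-4 | 17-25 | 21 |
| Visits 4-5 | 17-25 | 21 |
| Visits 5-6 | 25-31 | 28 |
| Visits 6-7 | 10-18 | 14 |
| Visits 7-8 | 28-38 | 35 |
| Visits 8-9 | 28-38 | 35 |

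The maximum is 31 days in Study Period II and 38 days in Study Period III.

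**Illustrative mean wait.** Assume that pregnancy becomes known at a uniformly random time, that visits fall on target, and that nobody stops drug earlier. The chance of falling in an interval of length L is L/ΣL and the mean remaining wait there is L/2, so the mean wait is ΣL²/(2ΣL).

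- Study Period II: (14² + 21² + 21² + 28²)/(2 × 84) = 1862/168 = 11.1 days.
- Study Period III: (14² + 35² + 35²)/(2 × 84) = 2646/168 = 15.75, or 15.8 days.

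**How much of that is atomoxetine.** In Study Period II the atomoxetine arm may start active drug as early as Visit 2 or as late as Visit 4 (Section 7.1).

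- Start at Visit 2: all 11.1 days.
- Start at Visit 4: only the last two intervals count, because a patient whose pregnancy is known earlier has left by Visit 4. (21 × 10.5 + 28 × 14)/84 = 612.5/84 = 7.3 days.
- Averaged over the two arms at 1:1, half of each: 3.6 to 5.5 days.

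In Study Period III all 15.8 days are on atomoxetine.

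**The case against.** The strongest reply is that the two sections are not linked. Section 8.2.1 explains entry exclusions, 8.3.1 does not cite it, and a site could give the undefined term its ordinary meaning and count pregnancy as a safety matter. The sorting in 8.2.1 is also loose: the compliance and confounding group holds earlier intolerable side effects on atomoxetine and uncontrolled thyroid disease, and a later paragraph gives a further rationale about conditions interacting with the drug. This stands as a limit. The finding is about the natural reading, not the only one. But where a timing rule turns on an undefined term, and the only guide to that term points the wrong way, the drafting is at fault.

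Second, the lead-in to 8.3.1 makes stopping drug mandatory, and the timing sentence speaks only of leaving the study. It could mean that drug stops at once and study exit follows at the visit. That reading is open, and no sentence tells a site to keep dosing. Equally, no sentence says drug stops earlier than study exit.

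Third, there are earlier routes out. The investigator, the patient, the attending physician or the sponsor can end participation, and [32], which is on the safety list, covers patients who "Are unsuitable in any way to participate in this study, in the opinion of the investigator". A positive serum test might also be handled as a clinically significant laboratory value. All of these are discretionary. The laboratory route starts with an investigator's decision, and [30] describes such abnormalities as those that, in the investigator's judgment, point to a serious medical problem. Many investigators would stop drug promptly, but the protocol does not require it.

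Finally, the consent pages and the Investigator's Brochure are not available here and may carry an instruction. The finding is therefore confined to the protocol text.

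**Conclusion.** The point holds, at minor severity. The protocol puts pregnancy outside its safety criteria, then ties the speed of discontinuation to that label, and nowhere requires study drug to stop immediately.

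The 31- and 38-day figures are the outer edges of the visit windows. The mean waits rest on a uniformly random time of discovery, the target schedule and no earlier action, so they illustrate scale and do not predict exposure. The protocol gives no pregnancy rate, so the number of patients affected cannot be estimated. Sample size, power and the analyses are unaffected.

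**What to change.** Move [17] from the compliance and confounding group to the safety group in Section 8.2.1. Add to Section 8.3.1:

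> Study drug is stopped as soon as pregnancy is known, without waiting for the next visit; end-of-study procedures follow.

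The second clause fits what 8.3.1 already provides: "Patients who discontinue the study early will have end-of-study procedures performed". The cost is wording in two sections, with no extra patients, visits or procedures and no change to the analysis.
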